### Statistical analysis

All primary analyses will be conducted separately by study city; Cape Coast, Chitungwiza and Mwanza. Where comparable, secondary analyses will be conducted with the data from all three cities combined.

In our study sites, a contemporaneous comparison group is not required since no routine screening is currently taking place, and as a result, assessments at baseline will serve as the counterfactual for internal comparisons. Similarly, since there is no routine screening and treatment provided to adolescents of the target ages in the study population, a before–after comparison is appropriate since it is plausible to assume that reductions in the prevalence of the chronic conditions between the original Y-Check visit and the follow-up at 4 months will be due to the interventions provided through Y-Check.

We will follow Strengthening the Reporting of Observational Studies in Epidemiology (STROBE) guidelines for the reporting of cohort studies. Descriptive analyses will be used to compare the community-level and school-level characteristics of the study communities and schools.

Quantitative programmatic data, including screening test results, services delivered and referrals made and completed will be reported by age, sex and city. The primary outcome is a single proportion which will be presented with a 95% CI for each of the four target groups: 10–14 year-old males, 10–14 year-old females, 15–19 year-old males 15–19 year-old females.

Secondary outcomes which are measured at a single-time point will be presented in a similar way to the primary outcome. For outcomes which are measured at two or more time points, a before–after analysis will be conducted comparing differences in measures between the time points. The unit of analysis will be the individual. For clinical outcomes which are measured at two or more time-points, the initial check-up visit (baseline) will give the prevalence of untreated conditions which will represent the counterfactual. The prevalence of conditions at the 4 month follow-up visit will be formally compared with this counterfactual to estimate the short-term effects of the intervention in improving these clinical outcomes. For analysis of outcomes measured at two timepoints, we will use mixed-effects logistic regression (binary outcomes) or linear regression (continuous outcomes) adjusting for individual-level clustering as a random effect and school/community as a fixed effect. Health service and client determinants of correct management of conditions at 4 months will be analysed using multivariable regression.

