### Study outcomes

Outcomes will be ascertained during the check-up screening visit and through collection of referral vouchers from the referral health facilities, and, for outcomes related to health and well-being impacts, through data from the 4 month and, in Zimbabwe only, 12 month follow-up visits. Outcomes related to completed referrals will be triangulated against participants’ self-reports at the 4 month and in Zimbabwe only, 12 month follow-up visits. Review of school and health service registers will be used to see whether attendance has increased during the period when Y-Check is being implemented.

The primary outcome will be the proportion of those screening positive for at least one condition who receive appropriate on-the-spot care or complete appropriate referral for all identified conditions within 4 months. This will be measured using data collected at the initial check-up visit and through recovery of referral vouchers given to participants to allow them to access referral services for free during the 4 months after the Y-Check screening. Completed referral is defined as attending at least the first referral appointment.

Secondary implementation outcomes will include the proportion of those screening positive for each condition who receive appropriate on-the-spot care or complete appropriate referral for that condition within 4 months, the yield of previously untreated conditions, clinical outcomes at 4 months among those who had originally screened positive for each condition, and intervention acceptability, adoption, appropriateness, feasibility, fidelity and cost. Secondary effectiveness outcomes will include knowledge about health services and health behaviours, self-reported agency and self-efficacy to make decisions about their health, self-reported health-related risk and protective behaviours, reported engagement with health services, well-being, self-esteem and quality of life, clinical outcomes and educational outcomes, which will be collected within the Y-Check and follow-up visits. The short-term cost-effectiveness of the intervention will be estimated (calculated by a comparison of the costs of the intervention against the primary and secondary outcomes and including short-term changes in self-reported quality of life). All outcomes for the study are described in table 3.

**Table 3 T3:** Study outcomes and means of verification

Outcome	Sources of data

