Evaluation of the Y-Check intervention will incorporate implementation science and effectiveness research. Such hybrid designs have important advantages over conducting separate studies. These include the potential for quicker translation of intervention research findings into programmes, the development and selection of more effective implementation strategies and more useful information for decision makers.^37^

The process evaluation findings will provide guidance for the next stage of the programme and for potential future sustainable and scalable implementation by local health authorities should it prove successful. Data on the short-term changes in clinical and behavioural outcomes will be used as inputs to model both short-term and long-term health and social impacts and as inputs to sample size and power calculations for a third phase of the Y-Check research programme, which plans to undertake a rigorous population level evaluation of the impact of routine check-ups on adolescent health and well-being.

Through WHO’s advice to member states, findings from the Y-Check study have the potential to shape the delivery of adolescent health check-ups globally including identifying the optimal number, content and delivery for these services. Y-Check will advance the field by providing some of the first rigorous information on the effects of a health screening programme in three African cities, assessing implementation, effectiveness, cost and cost-effectiveness outcomes.

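### For binary before–after outcomes the stated target is a change in prevalence, but the named mixed-effects logistic model yields a subject-specific odds ratio that is not that change and has no finite value when no new cases occur

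*Protocol article*

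**What the plan says.** All of the following is in the Protocol article, under Statistical analysis unless stated otherwise.

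- **Target.** For clinical outcomes measured more than once, the initial check-up "will give the prevalence of untreated conditions which will represent the counterfactual". Then: "The prevalence of conditions at the 4 month follow-up visit will be formally compared with this counterfactual". The general rule for repeated outcomes is that "a before–after analysis will be conducted comparing differences in measures between the time points". The argument for having no comparison group rests on "reductions in the prevalence of the chronic conditions between the original Y-Check visit and the follow-up at 4 months".
- **Estimator.** For outcomes at two time points, "we will use mixed-effects logistic regression (binary outcomes) or linear regression (continuous outcomes) adjusting for individual-level clustering as a random effect", with school or community as a fixed effect.
- **Single-time-point secondary outcomes.** These are presented like the primary outcome, which is a proportion with a 95% CI.
- **A related outcome.** Study outcomes lists "clinical outcomes at 4 months among those who had originally screened positive for each condition" among the secondary implementation outcomes.
- **Later use.** The Discussion says that data on short-term changes will serve, among other things, "as inputs to sample size and power calculations for a third phase" of the programme.

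The article names no effect measure for the binary before–after comparison (odds ratio, prevalence ratio or prevalence difference). It does not mention averaging over the random effect and gives no method for sparse or zero new cases.

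**The concern.** Prevalence is a population quantity, so a change in prevalence is a marginal effect. A logistic model with an individual random intercept estimates something else: the odds ratio for a given adolescent, holding that adolescent's own intercept fixed. For a linear model the two coincide, so continuous outcomes raise no issue. For a logistic model they do not, and they separate further as within-person correlation grows. Chronic conditions measured twice in 4 months are likely to be strongly correlated within person, with few adolescents newly affected. Analysing each city separately thins the new-case counts further.

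Two things follow. A reader told that prevalences are formally compared may take the model's odds ratio as the size of the prevalence change. And for a condition with no new cases, the named model produces no usable effect estimate at all.

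**Working it through.** **1. The plan's own figure.** The before–after analysis has no stated figure. The only computed one, under Sample size, concerns the primary outcome: 75% of 150, with a CI of ±7%. Check: 1.96 × √(0.75 × 0.25 / 150) = 0.069. It reproduces, and the primary outcome is not touched by this point.

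**2. What the coefficient estimates.** Let u be an adolescent's random intercept, p₁(u) = expit(a + u) at baseline and p₂(u) = expit(a + b + u) at 4 months. Then, for every u,

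P(new | u) / P(resolved | u) = [(1 − p₁)p₂] / [p₁(1 − p₂)] = exp(b).

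The ratio does not depend on u, so it survives averaging: exp(b) = P(new)/P(resolved). With two records per person and positive within-person correlation, the fitted odds ratio is therefore new cases divided by resolved cases. Numerical maximum likelihood agreed in all 30 paired tables tried. With eight schools as fixed effects it agreed to within 0.0002 in five of five simulated data sets (for example 8 new, 71 resolved: 0.1127 both ways). The school or community term does not alter the conclusion.

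**3. Worked example.** Assumed, not from the documents: 2000 adolescents (the city sample size), 10% baseline prevalence, 70% of cases resolved, 1% of negatives newly positive. Counts: 60 stay positive, 140 resolve, 18 new, 1782 stay negative.

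- Prevalence: 200/2000 = 10.0% to 78/2000 = 3.9%
- Prevalence ratio: 0.39
- Marginal odds ratio: (78/1922)/(200/1800) = 0.37
- Model odds ratio: 18/140 = 0.13, which is 0.365/0.129 = 2.8 times further from 1 than the marginal odds ratio
- Paired difference: −6.1 points; SE = √(158 − 122²/2000)/2000 = 0.0061; 95% CI −7.3 to −4.9

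**4. How the gap varies.** The article gives no per-condition prevalence, resolution rate or new-case rate, so a range is needed. Expected counts in a group of 500 with half of cases resolved:

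| Baseline | New among negatives | Model OR | Marginal OR | Marginal ÷ model |
|---|---|---|---|---|
| 30% | 0.5% | 0.023 | 0.423 | 18.1 |
| 30% | 2% | 0.093 | 0.458 | 4.9 |
| 30% | 5% | 0.233 | 0.530 | 2.3 |
| 30% | 10% | 0.467 | 0.658 | 1.4 |
| 10% | 0.5% | 0.090 | 0.519 | 5.8 |
| 10% | 2% | 0.360 | 0.657 | 1.8 |
| 10% | 5% | 0.900 | 0.945 | 1.05 |

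At 10% baseline with 10% new cases prevalence rises, and the model exaggerates the rise instead (1.80 against 1.47).

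**5. No new cases.** Take 75 stay positive, 75 resolve, 0 new, 350 stay negative. The log-likelihood keeps rising as b falls: −432.90 at b = −1, −410.77 at −4, −409.40 at −20, which is the saturated value. The fitted random-effect SD diverges with it (3.9, 7.9, 39). No finite estimate exists. The paired difference is unaffected: −75/500 = −15.0 points; SE = √(75 − 75²/500)/500 = 0.016; 95% CI −18.1 to −11.9.

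**6. Can the same model deliver the target?** Yes, when it converges. At 30% baseline, half resolved and 2% new, averaging the fitted probabilities over the random intercept returns 30.0% and 16.4%, the observed prevalences.

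**The case against.** The strongest reply is that the article names a model, not an effect measure. Nothing says the conditional odds ratio will be reported or read as the prevalence change. The same fitted model, averaged over its random effect, gives both prevalences, and an analysis plan that is not shown may specify exactly that. The formal comparison is also valid as a test: a conditional odds ratio of 1 means new equals resolved, which is the same null as equal prevalences, and with no new cases the likelihood stays bounded, so a likelihood-ratio comparison still exists. Finally, the subject-specific odds ratio is a legitimate answer to a different question, and mixed-effects logistic regression is standard for paired binary data.

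Most of this stands, and it limits the point. It does not remove it. The estimator is already fixed in the article beside a target stated as prevalence, and no step connects the two. Followed as written, the named model's coefficient is not the stated target. In a situation that is plausible for chronic conditions over 4 months, analysed by city, it cannot be estimated. That goes beyond detail left to another document.

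**Conclusion.** The mismatch between target and coefficient is real, and so is the absence of a finite estimate when no new cases occur. The size of the gap is conditional. Where prevalence falls, the model's odds ratio lies from about 1 to 18 times further from 1 than the marginal odds ratio over the assumed rates. The gap is several-fold only when new cases are rare: roughly 2% or fewer at 30% baseline, 1% or fewer at 10%.

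A reader might infer more than the documents support:

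- **That every binary effect will be overstated several-fold.** The new-case rates are assumptions. For self-reported behaviours or knowledge, movement in both directions is plausible and the gap may be small. The coefficient is not a biased prevalence ratio; it misleads only if read as one.
- **That the outcome among those who first screened positive cannot be estimated.** The before–after model would indeed fail there, since baseline is 100% by definition. But that outcome can be read as a single-time-point proportion, which the plan already presents with a 95% CI.
- **That the costing and phase-three inputs are compromised.** The Discussion refers to data on short-term changes, not to model odds ratios, and the raw prevalences and case counts remain available.

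The point concerns secondary binary outcomes only. It is worth correcting before analysis, but it does not threaten the primary result.

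**What to change.** For binary before–after secondary outcomes, state that the reported effect is the marginal within-person change in prevalence: the difference, and the ratio if wanted, with a 95% CI. Obtain it from GEE or a paired-proportion method, or by averaging the fitted mixed model over its random effect where that model converges. Name the paired difference as the method when new cases are zero or sparse. If the subject-specific odds ratio is kept, label it as such and report it as supplementary. Among adolescents who first screened positive for a condition, say explicitly that the 4-month proportion resolved will be reported with a 95% CI, in line with the existing single-time-point rule.

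The cost is a sentence or two in the analysis section or analysis plan and different standard code. No new data are needed. Reported effects may look smaller than the model's odds ratios would.

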### Intervention implementation

The intervention will be delivered over a period of 2–6 months in each of the settings. The follow-up visits will take place at the same school or community setting as the initial check-up. In addition to covering all clinical costs, the equivalent of US$5 will be given to each participant who attends the follow-up to cover any transport costs that they might have incurred. Additionally, health and hygiene related items will also be provided for adolescents to take home, including tooth cleaning kit (toothbrush and toothpaste), fruit, bottle of water, two pairs of underpants and pack of reusable sanitary pads (girls only).

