### Sample size

In each city, the intervention will be implemented for 10–14 year olds in up to six government primary schools (n=500 for young adolescent girls, and n=500 for young adolescent boys), and for 15–19 year-olds in up to eight secondary schools and up to three community venues (n=500 for older adolescent girls, and n=500 for older adolescent boys), giving a total sample size of 2000 adolescents (10–19 y).

The sample size provides specified precision around the primary outcome. For example, for the primary outcome, within each age group and gender, if 150 (30%) of 500 participants screen positive for at least one condition, and 75% of those who screen positive are correctly managed (n=112), the 95% CI for correct management will be ±7%. The primary outcome used data from the initial check-up visit and referrals and did not require the 4 month follow-up data.

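### The before–after model enters school/community only as a fixed intercept, so standard errors are too small for any outcome whose change is correlated within school or venue

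*Protocol article*

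**What the plan says.** The Statistical analysis section of the protocol article states that "The unit of analysis will be the individual" and that, for outcomes with two or more time points, "a before–after analysis will be conducted comparing differences in measures between the time points". For outcomes measured at two time points, the model is mixed-effects logistic regression (binary) or linear regression (continuous), "adjusting for individual-level clustering as a random effect and school/community as a fixed effect". For clinical outcomes, baseline prevalence serves as the counterfactual: "The prevalence of conditions at the 4 month follow-up visit will be formally compared with this counterfactual". On level of analysis, "All primary analyses will be conducted separately by study city; Cape Coast, Chitungwiza and Mwanza".

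The same section, as published, names no site-by-time term, no random effect of site on change and no cluster-robust standard error. On conduct, the Intervention implementation section says "The follow-up visits will take place at the same school or community setting as the initial check-up". The Sample size section gives 2000 adolescents per city, in up to six primary schools, up to eight secondary schools and up to three community venues.

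**The concern.** The sentence reads as if clustering by school had been dealt with. It has been dealt with for differences in level between sites, but not for differences in change, and change is what the before–after analysis estimates.

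Correlated change within site is plausible from what the article does say. Baseline and follow-up take place at the same site, and delivery is spread over 2–6 months in each setting, so calendar period may differ between sites. In Mwanza, schools are chosen within the catchment of facilities serving the selected communities (Table 2).

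At stake are the confidence intervals and p-values for secondary outcomes such as knowledge, behaviour, well-being and clinical change. The Discussion carries the short-term clinical and behavioural changes into modelling of longer-term impact and into sample sizes for the next phase. Intervals that are too narrow would be carried along.

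A smaller point concerns scale. The text says prevalences are compared, but a logistic model with an individual random effect estimates a subject-specific odds ratio, which is not the change in prevalence.

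**Working it through.** **1. The plan's own precision figure.** The Sample size section gives ±7% for 150 screen-positives with 75% correctly managed: 1.96 × √(0.75 × 0.25 / 150) = 0.0693, or 6.9 points. It reproduces. It concerns the primary outcome, a single proportion outside this model. The article states no precision for the before–after outcomes.

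**2. Why the fixed intercept drops out.** Write the stated model for person i in site j at visit t (0 or 1) as y = α_j + b_i + τt + e. The within-person change is d = τ + (e₁ − e₀); both α_j and b_i have gone. With complete pairs, the standard error of τ is SD(d)/√n. If sites truly differ in change, d = τ + u_j + error, and the variance of the mean change is larger by

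DE = 1 + (m − 1)ρ,

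where m is the number per site and ρ is the ICC of change.

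Two mixed-model fits to simulated continuous data confirm this:
- 6 sites of 40 with real between-site variation in change: the standard error of the time effect was 0.0893 with the site term, 0.0893 without it, and 0.0893 from simple paired differences.
- A second fit gave 0.0801 with site fixed effects, equal to the paired value of 0.0801, against a site-level standard error of 0.129.

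**3. Inputs.**
- Per city (Sample size section): n = 2000; 6 + 8 + 3 = 17 sites at most; m = 2000/17 ≈ 118.
- Cape Coast (Table 2): 8 schools + 4 communities = 12 sites; m ≈ 167.
- Mwanza (Table 2): up to 8 + 8 + 6 = 22 sites; m ≈ 91.
- Screen-positive subset in one age–sex group: 150 over 6 to 11 sites; m ≈ 25 to 14.
- Assumed, because the article does not give them: ρ from 0 to 0.05, two-sided 5% tests, equal site sizes, complete follow-up.

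**4. True type I error of a nominal 5% test** = 2[1 − Φ(1.96/√DE)]. For 17 sites at ρ = 0.01: DE = 1 + 116.6 × 0.01 = 2.17; √2.17 = 1.47; 1.96/1.47 = 1.33; type I error = 18%.

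| ρ (assumed) | 17 sites, m ≈ 118 | 12 sites, m ≈ 167 | 22 sites, m ≈ 91 | Screen-positives, m ≈ 25 | Screen-positives, m ≈ 14 |
|---|---|---|---|---|---|
| 0 | 5.0% | 5.0% | 5.0% | 5.0% | 5.0% |
| 0.001 | 6.4% | 6.9% | 6.0% | 5.3% | 5.1% |
| 0.005 | 11.9% | 14.7% | 10.4% | 6.4% | 5.7% |
| 0.01 | 18.3% | 22.9% | 15.5% | 7.8% | 6.5% |
| 0.02 | 28.3% | 34.5% | 24.1% | 10.7% | 8.0% |
| 0.05 | 45.3% | 52.0% | 40.3% | 18.6% | 12.5% |

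**5. Simulation checks.**
- Continuous change, 17 × 118: the paired test rejected in 5.2%, 19.2% and 45.3% of runs at ρ = 0, 0.01 and 0.05, in line with the formula. A t-test on site mean changes with (sites − 1) degrees of freedom stayed at 4.4–5.5% across all continuous settings.
- Paired binary outcome, using McNemar's test as a stand-in for the mixed logistic model: with a between-site SD of change on the logit scale of 0, 0.1, 0.2 and 0.3, rejection was 4.7%, 6.5%, 9.0% and 14.1% (17 × 118).

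**6. Scale of the binary effect (illustrative figures).** Let prevalence fall from 20% to 15%, with 8% resolved and 3% new. The prevalence odds ratio is (0.15/0.85)/(0.20/0.80) = 0.71. The matched-pair odds ratio, which like the mixed model's is subject-specific, is 3/8 = 0.375. The prevalence difference is −5 points.

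**The case against.** **Inflation is conditional.** A reader might infer that the false-positive rate is inflated for every two-time-point outcome. The article does not support that. It gives no ICC of change; at zero the test is correct and at 0.001 the error is 6–7%. Nor does it say that pupils of one school share a team, the same weeks or a referral facility. It speaks of teams in the plural and of referral close to the adolescent's home. Correlation within site is plausible but not documented. This objection stands, and it limits the claim to outcomes whose change is in fact correlated.

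**Fixed effects can be right for few, chosen sites.** Mwanza's communities are purposively selected. If inference stops at the sites studied, real differences in change between them are not sampling error. This has force in principle, but the article does not stop there. The strengths and limitations box says findings can be applied to programmes, and the Discussion uses the changes for modelling and later sample sizes. The Statistical analysis section attributes falls in chronic conditions to Y-Check without a comparison group. For that purpose, site-specific shocks over time are noise even within the chosen sites.

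**A fuller plan may add robust standard errors.** It may. But the point is not an omission: the article states how school/community enters the model, and that choice leaves the error bars as shown.

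**Neighbouring points.** A reader might extend the criticism to the determinants analysis, where "Health service and client determinants of correct management of conditions at 4 months will be analysed using multivariable regression". That clause neither states nor excludes a method for clustering, so no fault can be shown. A reader might also count the odds ratio as a false-positive problem. It is not: it concerns the reporting scale, and nothing says that prevalences will go unreported.

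**Conclusion.** The point holds in a conditional form. As published, the model makes no allowance for between-site variation in change, so standard errors are too small for any two-time-point outcome whose change is correlated within school or venue. Because sites are large, a small correlation is enough for outcomes measured in everyone: at an assumed ICC of 0.01 the standard error should be about 1.47 times larger with 17 sites per city, and the true type I error is about 18% (about 23% with 12 sites, 15–16% with 22). For outcomes confined to screen-positives it is only about 6.5–8% at the same ICC.

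These figures rest on the assumed ICC, equal site sizes, complete follow-up and a 5% two-sided test. The real inflation will differ by outcome and could be negligible for some.

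A reader might infer that the primary outcome or its ±7% is undermined by this model. It is not: the primary outcome is a single proportion, uses no 4-month follow-up data and is not analysed by this model. The affected outcomes are secondary, in a study that declares its pre–post limitation. This should be fixed before analysis, but it is not a fatal defect.

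**What to change.** Amend the sentence on two-time-point outcomes in one of these ways:
- keep the individual random effect and add a school/venue-by-time random effect;
- fit a marginal model (GEE or linear) clustered on school/venue;
- analyse site-level mean changes.

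In each case use a small-sample correction, with t on the number of sites minus 1 degrees of freedom, because there are only about 12 to 22 sites per city and fewer within an age group. State whether inference is meant for the sites studied or beyond them.

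For binary outcomes, report the marginal prevalence difference with its interval alongside any subject-specific odds ratio, since the text says prevalences are compared.

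The cost is about one sentence in the analysis section and standard software options. No new data are needed. The downside is wider intervals, most of all for outcomes measured in all adolescents and for age groups with few sites.
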